**Management**		
Equipment	Downtime due to technical issues of VR equipment	> 85% of subjects without any downtime
Processing time	Time from initial contact to enrolment	Mean time is < 5 days
**Scientific**		
Safety	Adverse events from the program activities/advice, or assessments	No major injuries or adverse events reported
Treatment response	ANCOVA comparison between groups	Significant group difference in primary clinical outcome
Treatment effect	Estimate of effect size and variance for future sample size calculations	Data on all relevant variables

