### Patient population and sample size

A total of 30 volunteer participants who are receiving inpatient stroke rehabilitation with an expected length of stay of at least 14 days in the rehabilitation unit at Kelowna General Hospital will be recruited. A sample size of 30 is recommended for robust feasibility data used to inform larger trials [51]. Individuals will be included in the study if they have a diagnosis of stroke confirmed by CT scan or MRI; 19 years of age or older; able to provide informed consent; physician clearance to participate in the study (including consideration of cognitive ability, mood (e.g., clinical depression), and functional ability); able to understand English. Individuals will be excluded if they have a visual or hearing impairment that limits engagement in the VR entertainment program; planned surgical procedure, not medically stable, severe aphasia, or have significant musculoskeletal or other neurological conditions.

Enrolled participants will meet with a trained and blinded study assessor who will administer each of the outcome measures, at two timepoints: (i) baseline (T1) and (ii) post-intervention (T2). Each participant will meet with the same study assessor at both time points to ensure consistency in the administration of outcome measures.

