### Randomization and interventions

After baseline evaluation, participants will be randomly assigned (1:1) to either: the usual care control group, or the VR experimental group. A statistician not involved with the research study will generate the randomization algorithm and provide the research team with sealed envelopes containing the group allocation for sequential participants. An unblinded research coordinator will open the envelope and advise the participants of which group they have been randomized to and advise them of the next steps.

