#### Feasibility outcomes

Study-specific feasibility criteria have been developed related to process, resources, management, and scientific assessment (Table 1). Feasibility indicators will be dichotomized into either ‘success’ if they meet the a priori criteria, or ‘revise’ if they do not meet the criteria. ‘Success’ will indicate that the protocol is sufficient to move forward with a larger RCT with only small or no adaptation required, and ‘revise’ indicate a need for changes before proceeding.

**Table 1 Tab1:** Feasibility indicators

Feasibility	Indicator	Criteria for success

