#### Clinical outcomes

Intervention effects post-intervention (T2) for the primary and secondary clinical outcomes will be estimated using linear regression including baseline (T1) controlling for age and sex. All analyses will be intention-to-treat. Missing data will be assessed and analysed as appropriate. Analyses will be performed using R software (R Foundation, Vienna) with a significance at 0.05.

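### A p<0.05 difference on HADS-D is a feasibility success criterion in a trial not sized for it, so a true small-to-moderate benefit would usually be labelled 'revise'

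*Protocol article*

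**What the plan says.** Four places in the Protocol article bear on this.

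- **Table 1, Scientific block.** The 'Treatment response' row is assessed by an ANCOVA comparison between groups. Its criterion for success is "Significant group difference in primary clinical outcome". The row below it, 'Treatment effect', asks for an effect size and variance to plan a later trial.
- **Feasibility outcomes.** Every indicator is dichotomised. 'Success' means that the protocol can go forward to a larger RCT with little or no adaptation. 'Revise' is said to "indicate a need for changes before proceeding". No row of Table 1 is exempted.
- **Patient population and sample size.** The only justification for the number is that "A sample size of 30 is recommended for robust feasibility data used to inform larger trials". No effect size, SD or power is given.
- **Clinical outcomes.** The T2 outcome is regressed on group with baseline, age and sex as covariates, "with a significance at 0.05". The sidedness of the test is not stated.

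The Background names sufficient feasibility for a larger RCT as the primary hypothesis.

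**The concern.** The sample size was set for one purpose and the criterion belongs to another. A feasibility sample is meant to show whether recruitment, retention, delivery and measurement work, and to supply variance estimates. A significance test on the clinical outcome answers a different question, and with about 15 per arm its answer depends heavily on the sample size. When such a test fails, the plan reads the failure as a sign that the protocol needs changes, although the protocol may have worked exactly as intended.

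At stake is the meaning of one a priori indicator feeding the trial's main conclusion. A sound protocol could be marked for revision because the pilot was small. Removing a failed criterion after the results are known would look post hoc, so the time to deal with it is before then.

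A smaller wording point: the criterion has no direction, so read literally a significant difference in favour of usual care would also satisfy it.

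**Working it through.** **The plan's own figure.** N = 30 rests on a feasibility convention, so there is no power calculation to reproduce. The check is what power N = 30 gives for the test named in Table 1.

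**Inputs from the Protocol article**
- N = 30 (Patient population and sample size); "participants will be randomly assigned (1:1) to either: the usual care control group, or the VR experimental group" (Randomization and interventions), hence 15 per arm.
- Significance level 0.05; three covariates: baseline, age and sex (Clinical outcomes).
- Retention criterion of more than 80% (Table 1, Process). At that threshold 0.80 × 30 = 24, or 12 per arm, are analysable. This is a lower case, not a forecast.

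**Assumptions, not in the article**
- Two-sided test.
- Standardised effect d (difference divided by the SD of HADS-D at T2) of 0.3, 0.5 or 0.8.
- Baseline–T2 correlation r from 0 to 0.7, with age and sex explaining nothing further.

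**Formula.** With n per arm, the noncentrality parameter is δ = [d / √(1 − r²)] × √(n/2), with df = 2n − 2 − 3 = 2n − 5. Power is the probability that a noncentral t with these parameters exceeds the two-sided 5% critical value in absolute size.

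**Worked case, d = 0.5, r = 0.5**
- 15 per arm: δ = (0.5/0.866) × √7.5 = 0.577 × 2.739 = 1.58; df = 25; critical t = 2.06; power = 33%.
- 12 per arm: δ = 0.577 × √6 = 0.577 × 2.449 = 1.41; df = 19; critical t = 2.09; power = 27%.

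**Power over the range**

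| d | n per arm | r = 0 | r = 0.5 | r = 0.6 | r = 0.7 |
|---|---|---|---|---|---|
| 0.3 | 15 | 12% | 15% | 17% | 20% |
| 0.3 | 12 | 11% | 13% | 14% | 17% |
| 0.5 | 15 | 26% | 33% | 38% | 45% |
| 0.5 | 12 | 21% | 27% | 31% | 37% |
| 0.8 | 15 | 56% | 68% | 75% | 84% |
| 0.8 | 12 | 46% | 57% | 64% | 74% |

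**Chance of 'revise' on this row when d = 0.5 is true** (100% minus power)
- 15 per arm: 100 − 45 = 55% to 100 − 26 = 74%.
- 12 per arm: 100 − 37 = 63% to 100 − 21 = 79%.

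**Where the likelier label switches.** Power reaches 50% at the following d:
- 15 per arm: 0.74, 0.65, 0.60 and 0.53 for r = 0, 0.5, 0.6 and 0.7.
- 12 per arm: 0.84, 0.73, 0.67 and 0.60.

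Below these values 'revise' is the likelier label; above them 'success' is.

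**Size needed for the criterion to have 80% power**
- d = 0.5: 64, 49 or 42 per arm for r = 0, 0.5 or 0.6.
- d = 0.3: 176, 132 or 113 per arm.

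The trial has 15 per arm.

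**If VR has no effect.** The criterion is still met 5% of the time, and half of that (2.5%) is in favour of usual care.

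**The case against.** The best case for leaving the row alone has four parts.

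1. *The effect might be large.* This part stands as a limit. At d = 0.8 'success' is the likelier label in every case tried except 12 per arm with r = 0 (46%). A reader might infer that the criterion will most likely return 'revise' whenever VR works. The article does not support that, because it states no expected effect, and the answer turns at d of about 0.53–0.74 with 15 per arm.

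2. *One row does not decide the trial.* This also stands. Table 1 has 11 indicators, the only outcomes are 'success' and 'revise', and nothing says how the rows combine. A reader might infer that a non-significant result stops progression to a larger RCT. The text has no stop outcome; it supports only that changes would be called for. This does not rescue the row, because its label says little about feasibility however the rows are combined.

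3. *The missing direction is harmless in practice.* Largely true. A reader might infer that the rule rewards harm. The aim of improving depressive symptoms makes the intended direction plain, safety has its own row, and a significant result favouring usual care has a chance of 2.5% if VR does nothing and less if it helps. It is a wording gap.

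4. *The useful estimate is collected anyway.* Correct: the 'Treatment effect' row already asks for it. That argues for removing the significance criterion, since the later trial loses nothing by it.

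Nor is this a detail that a fuller plan might settle: the article itself states both the criterion and its consequence.

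**Conclusion.** The point holds in conditional form. A significance criterion has been placed among the feasibility rules of a trial whose size was not chosen to support it. For small-to-moderate true effects (d up to about 0.5) 'revise' is the likelier label in every scenario tried, at about 55–79% for d = 0.5. For large effects this is generally not so.

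The figures rest on a two-sided test, the assumed effects and correlations, and 12 to 15 analysable participants per arm. The structural point, that the label mainly reflects sample size, does not depend on any single one of these values.

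It should be fixed, but it is not critical. Recruitment, randomisation, data collection and the estimate handed to a later trial are unaffected, and one of 11 indicators is mislabelled.

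**What to change.** - Delete the significance requirement as the success criterion for 'Treatment response' in Table 1.
- Report the adjusted HADS-D difference (VR minus usual care) with its 95% CI and the SD, as the 'Treatment effect' row already intends.
- Add one sentence under Feasibility outcomes saying that p-values for the clinical outcomes do not enter the success/revise decision.

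No other efficacy-based rule should take its place. A tempting one is to require that the point estimate does not favour usual care and that the CI does not exclude a clinically important benefit. The CI half-width is t × √(1 − r²) × √(2/n). With 15 per arm that is 2.06 × 0.365 = 0.75 SD at r = 0 and 0.75 × 0.714 = 0.54 SD at r = 0.7. With 12 per arm it is 2.09 × 0.408 = 0.85 SD and 0.85 × 0.714 = 0.61 SD. For any important benefit smaller than the half-width, the CI clause adds nothing once the estimate does not favour usual care. The rule then reduces to the sign of the estimate, and a useless intervention passes about half the time. It would also keep efficacy as a feasibility gate.

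The cost is one table row and one sentence, with no extra participants or data. The trial gives up a significance-based success claim that it is not sized to support.

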#### Clinical outcomes

Intervention effects post-intervention (T2) for the primary and secondary clinical outcomes will be estimated using linear regression including baseline (T1) controlling for age and sex. All analyses will be intention-to-treat. Missing data will be assessed and analysed as appropriate. Analyses will be performed using R software (R Foundation, Vienna) with a significance at 0.05.

## Discussion

The results of this study will increase our understanding about VR, depressive symptoms and sedentary behaviour among individuals receiving inpatient stroke rehabilitation. The information gathered may be used to benefit future patients. Furthermore, if the results are as hypothesized, the protocol will demonstrate sufficient feasibility to support a subsequent larger RCT to examine the effect of VR on depressive symptoms and sedentary behaviour among inpatient stroke survivors. Also, this study will provide insight into how decreased sedentary behaviour during inpatient rehabilitation will affect stroke patient’s sedentary behaviour post inpatient rehabilitation. With depression being a prominent issue in stroke survivors, VR could potentially provide another method to increase activity for stroke survivors.

## Data Availability

Data and study materials will be made available upon reasonable request to the corresponding author.

## Abbreviations

PSD: Post-stroke depression
VR: Virtual reality
HMD: Head-mounted display
RCT: Randomized controlled trial
